### Statistical analysis

The researchers will be aware of allocation to early surgery or conservative treatment at the time of the statistical analyses. There will be an intermediate analysis after 2 years of follow up. The intermediate outcome measures are progression of AAS and VT with or without (pain) complaints and neurological disability (measured with the MDI and Ranawat). The main analyses will be performed after 5 years and 10 years of follow up. At these intervals the primary outcome parameter is the occurrence of an event as described in table 5. Baseline comparability will be investigated by descriptive statistics to examine if randomization was successful. Differences in success rates between both groups are calculated, together with 95 percent confidence intervals. In addition to an analysis of the difference in outcome between the two groups analyses of the difference in time to progression will be carried out. Continuous outcomes are evaluated as change scores (differences between baseline measurement and each follow-up measurement). Multivariable analyses are performed to adjust for the eventual differences between the groups at baseline in prognostic indicators. All the analyses are performed according to the intention-to-treat principle. An additional per protocol analysis will be performed comparing patients in the conservative group who received surgery with patients in the same group who had not and with patients in the surgery group. To compare the actual treatment sec instead of strategies an explorative analysis will be performed in subgroups of all patients who actually received surgery and who did not receive surgery in both groups. All patients withdrawn from the study are included in the analysis until the time of withdrawal.

To answer the third research question, explorative analyses are conducted to investigate whether the treatment effect varies in specific subgroups of patients. Using logistic regression for success rate and linear regression for severity of the disability, each prognostic indicator is checked for interaction with treatment.

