The spinal column consists of vertebrae stabilized by an intricate network of ligaments. Especially in the cervical spine, rheumatoid arthritis can cause degeneration of these ligaments, causing laxity, instability and subluxation of the vertebral bodies. Subsequent compression of the spinal cord and medulla oblongata can cause severe neurological deficits and even sudden death. Cervical spine involvement typically begins early in the disease process, and its progression has been closely correlated with the extent of peripheral disease activity [4-6]. Several types of subluxations have been described [3]. The first signs and symptoms of atlantoaxial instability are the result of rheumatoid synovial proliferation. Because of erosions of the transverse, apical and alar ligaments an anterior atlantoaxial subluxation (AAS) develops. Damage to the transverse ligament alone will allow approximately 3 to 4 mm of subluxation; a greater anterior atlanto dental interval (AADI) implies damage to the alar-apical ligament complex, an incomplete odontoid peg or a resorbed dens [4]. The average duration of RA at the onset of AAS has been reported being 12.7 years (3–26 years) [7]. Many patients acquire AAS in the first 3 years of their disease, but neurological impairments develop after a mean period of 18 years (range 4–50 years) [8]. When the odontoid process erodes a posterior AAS can evolve. Vertical Translocation (VT) (Cranial settling, basilar invagination, or superior migration of the odontoid process) results from progressive destruction of the lateral mass joints (atlantoaxial and occipitoatlantal) and the lateral masses themselves, as a result of chronic craniocervical instability [9-11]. The odontoid process moves towards and beyond the borders of the foramen magnum. Secondarily periodontoid pannus is formed in reaction to the chronic instability [3,12]. VT is observed in 4–35% of patients [13]. Because of VT the AADI can decrease, which virtually is a paradoxal improvement [9,14,15]. VT appears after a mean of 16.5 years (4–33 years) after the onset of the RA inflammatory process and almost exclusively after the onset of AAS [8,16]. Involvement of the subaxial spine (SAS) is less common, occurs later in the course of the disease, and manifests as multilevel anterior dislocation (7–29%) [13].

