## Design

An international multicenter randomized clinical trial will be performed. Centers in the Netherlands (table 1), Belgium, Denmark, France, Germany, Italy, Latvia, Portugal, Spain, Sweden, Switzerland, United Kingdom, USA and Canada will participate (table 2 and figure 1 and 2). The multicenter design is necessary to recruit all patients in the inclusion period of 2 years. Early surgery will be compared with prolonged conservative treatment. The selection and randomization procedure is depicted in figure 3. The overall range for randomization of the AAS is an AADI between 5–12 mm. Participating centers/countries are allowed to randomize different intervals of subluxation. The intervals are predefined as 5–8 mm, 5–12 mm and 8–12 mm. Demographic and clinical data will be collected of each patient. The randomization of all patients will be performed centrally at the LUMC by the trial coordinator and datamanager by a concealed randomization list in random permuted blocks.

After a follow up of 5 years the main research question will be answered, although the total follow-up will be 10 years. Patients excluded from the trial will be followed in a cohort group and treated according to the usual care by surgical fixation or conservative treatment. The LUMC will function as the research and data coordinating center, where the data will be collected, analyzed and publications prepared. Eligibility criteria will differ from site to site, according to local perceptions of equipoise. These efforts will increase the generalization of the results. The authors have full access to the data, direct the data-analysis and are responsible for decisions regarding publication. The principal investigator and the trial coordinator assume full responsibility for the integrity and interpretation of the data.

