### Sample size/power calculation

The sample size is calculated on the basis of the outcome difference during the follow-up period of at least 5 years. Hypothetically, 8% of included patients will worsen in the 5 year follow up period resulting in an event (Kaplan Meier) (16,21). In the early surgery group the event rate is expected to be 2% or less [44]. 2% is chosen because it has to be a save alternative to 'wait and see'. A two-sided log rank test with an overall sample size of 250 patients, achieves 90% power at a 0.05 significance level to detect a difference in groups 1 and 2 after 5 years of follow up. Patients enter the study during an accrual period of 2 years. 50% of the enrolment is complete when 50% of the accrual time has past. A follow-up period of 5 years with a 20% loss from group 1 and a 20% loss from group 2 is calculated.

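### The main question is to be answered at 5 years, yet the 5- and 10-year analyses of the same primary outcome are both called main, which leaves the 0.05 level unprotected

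*Protocol article*

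**What the plan says.** Three sections of the protocol article bear on when the trial's main comparison is made.

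- **Design:** "After a follow up of 5 years the main research question will be answered, although the total follow-up will be 10 years". This gives one deciding time, with follow-up continuing beyond it.
- **Sample size/power calculation:** "A two-sided log rank test with an overall sample size of 250 patients, achieves 90% power at a 0.05 significance level", and the aim of that test is "to detect a difference in groups 1 and 2 after 5 years of follow up". The level and the power are thus both attached to 5 years.
- **Statistical analysis:** "The main analyses will be performed after 5 years and 10 years of follow up", followed by "At these intervals the primary outcome parameter is the occurrence of an event as described in table 5". Two analyses of one outcome have the same rank.

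The Statistical analysis section also plans a look at 2 years, on separately named intermediate measures. For reporting it says: "Differences in success rates between both groups are calculated, together with 95 percent confidence intervals". It gives no order between 5 and 10 years, no division of the significance level, and no rule for the case where the two results differ.

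**The concern.** The article addresses the deciding time in two places and gives two answers. An analysis plan that tests at 5 years only and one that tests at both times could each claim to follow it.

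Two things are at stake. The first is the error rate: testing the same hypothesis twice at 0.05, with either result able to carry the conclusion, gives an overall level above 0.05. The second is that the deciding time could be chosen late. The 5-year result will be known about five years before the 10-year one, and the Statistical analysis section says the researchers will know the allocation when they analyse. If the two results differ, either could be presented as the main answer.

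**Working it through.** **Step 1. The plan's own figure.** With one two-sided test at 5 years and critical value 1.96, the type I error is 0.05, as stated. The 90% power attached to it was also tried. For 8% against 2% at 5 years, the hazard ratio is ln(0.98)/ln(0.92) = 0.242. With 250 patients (1:1 assumed), uniform 2-year accrual, 5 further years of follow-up and 20% loss, about 13.1 events are expected. Power is then 73% (Schoenfeld) or 60% (Freedman), so 90% is not reproduced. That is a separate matter and does not affect the type I error below.

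**Step 2. Share of the 10-year events seen by year 5.** Inputs from the Sample size/power calculation section are 8% and 2% events by 5 years, and 20% loss per arm over 5 years. Under the null hypothesis take the average event rate, (8% + 2%)/2 = 5%. Two assumptions are added: constant hazards, and a further 20% loss in years 5 to 10.

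- Event hazard h = −ln(0.95)/5; loss hazard l = −ln(0.80)/5.
- Proportion with an observed event by time T: F(T) = h/(h + l) × [1 − exp(−(h + l)T)].
- At 5 years the exponential is 0.95 × 0.80 = 0.76. At 10 years it is 0.76² = 0.5776.
- Share t = F(5)/F(10) = (1 − 0.76)/(1 − 0.5776) = 0.24/0.4224 = 0.568.

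In 250 patients this is about 11.2 events by year 5 and 19.7 by year 10. Keeping 8% and 2% in separate arms gives 11.2 and 19.6 (share 0.57). Without any loss it gives 12.5 and 24.2 (share 0.52).

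**Step 3. Overall type I error if either time may decide.** The 10-year analysis contains the 5-year events, so the two test statistics are correlated, with correlation √t. The error is 1 − P(|Z₁| ≤ 1.96 and |Z₂| ≤ 1.96) for a bivariate normal pair.

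| Share of events by year 5 | Overall type I error |
|---|---|
| 0.3 | 0.089 |
| 0.4 | 0.086 |
| 0.5 | 0.083 |
| 0.57 (central) | 0.081 |
| 0.6 | 0.080 |
| 0.7 | 0.076 |
| 0.8 | 0.071 |

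Two independent tests would give 1 − 0.95² = 0.0975, which is an upper limit.

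**Step 4. Level that would restore 0.05.** Solving the same expression for an equal nominal level at both times gives 0.0294 at a share of 0.50, 0.0300 at 0.55 and 0.0307 at 0.60, so about 0.030 at each. An O'Brien-Fleming split at a share of 0.50 would be about 0.005 at 5 years and 0.048 at 10 years.

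**The case against.** The strongest reply is that the article already settles the matter. The Design section answers the main question at 5 years, and the level and power are given for 5 years only. The word main in the Statistical analysis section may simply contrast with the intermediate analysis at 2 years. That section names no significance level for 10 years and speaks of differences with 95% confidence intervals. An alpha split or testing order is also commonly left to the statistical analysis plan, which is not shown.

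Much of this stands. It is the most natural way to reconcile the sections, and under it the level is 0.05. The absence of an alpha split is not itself the point. What does not go away is that the Statistical analysis section, as worded, gives both times equal rank on the same primary outcome. The conflict is in the stated text.

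A reader might infer more than the article supports:

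- **That the 0.05 level is broken.** This needs a test at 0.05 at both times and success declared on either. The article says neither.
- **That the 2-year look adds a third test.** It has its own intermediate measures, and no efficacy claim is attached to it.
- **That slow disease makes the 5- and 10-year results likely to disagree.** The mean of 18 years to neurological impairment in the Background most naturally runs from onset of rheumatoid arthritis. Enrolled patients already have subluxation, and the primary event also includes radiological progression, surgery, resurgery and death.
- **That conservative patients will be operated on because of the 5-year result.** The Conservative treatment section gives failure of conservative management as the indication for surgery. No section describes surgery prompted by the trial's result.

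**Conclusion.** The point holds as an inconsistency with a conditional consequence. Two sections make 5 years decisive, and a third ranks 5 and 10 years equally on the same outcome, so nothing in the article protects the 0.05 level.

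If both times are tested at 0.05 and either may decide, the overall type I error is about 0.08. Constant hazards and the second 20% loss lie behind the central share of 0.57, but the conclusion depends little on them: across shares of 0.8 to 0.3 the error stays between 0.071 and 0.089. With roughly 11 and 20 events, the normal approximation is itself rough. If 5 years alone decides, the error is 0.05 and only the wording needs repair. The correction is still worth making, because it removes the chance to choose the deciding time once the 5-year result is known.

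**What to change.** In the Statistical analysis section, name the 5-year comparison of the primary event as the single confirmatory analysis, in line with the Design and Sample size/power calculation sections. Describe the 10-year analysis as long-term follow-up, reported as estimates with confidence intervals. This takes one or two sentences and changes no data collection. The downside is that the 10-year result loses confirmatory status.

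If both times are meant to be confirmatory, state an alpha split instead, such as about 0.030 at each time. This has a cost in power at 5 years. Taking the stated 90% at face value, the standardised effect is 1.960 + 1.282 = 3.242. The critical value at 0.030 is 2.170, and 3.242 − 2.170 = 1.072 corresponds to about 86% power.

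### The trial is sized on a log-rank test of a composite event, but the analysis section leads with a difference in success rates and does not tie its time-to-event analysis to that composite

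*Protocol article*

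**What the plan says.** **Sizing.** The section Sample size/power calculation of the Protocol article states: "A two-sided log rank test with an overall sample size of 250 patients, achieves 90% power at a 0.05 significance level". The conservative-arm rate is 8% over 5 years, labelled a Kaplan-Meier quantity. For the other arm, "In the early surgery group the event rate is expected to be 2% or less". On loss: "A follow-up period of 5 years with a 20% loss from group 1 and a 20% loss from group 2 is calculated".

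**Outcome.** The primary outcome is the occurrence of an event. The event has five components: neurological deficit, radiological progression, surgery, resurgery and death.

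**Analysis.** For the main analyses at 5 and 10 years, the Statistical analysis section gives the group comparison as: "Differences in success rates between both groups are calculated, together with 95 percent confidence intervals". The next sentence adds, as a supplement, an analysis of time to progression, with no method named. On withdrawals: "All patients withdrawn from the study are included in the analysis until the time of withdrawal". For the exploratory third research question, subgroup interactions are examined: "Using logistic regression for success rate and linear regression for severity of the disability". The section also says that the researchers will know the allocation when they analyse the data. It does not mention the log-rank test, Kaplan-Meier estimation or Cox regression.

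**The concern.** The test that justifies the sample size should be the test that decides the trial. Here the link is loose in three places.

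1. The comparison listed first is a difference in success rates, and the log-rank test is not carried over from the sizing.
2. The time-based analysis concerns progression. In this protocol that word names one of the five event components. For the 2-year analysis it means progression of the subluxation and of the vertical translocation. Nothing says that it stands for the composite.
3. The withdrawal rule is a censoring rule. A 5-year proportion cannot use partial follow-up: each lost patient has to be called a success, called a failure, or left out.

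At stake are an estimate that depends on how lost patients are handled, and a choice between analyses left open to analysts who know the allocation.

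**Working it through.** **Inputs from the protocol:** 8% and 2% event rates over 5 years, 20% loss per arm, 250 patients, two-sided 5% level. **Assumptions:** 1:1 allocation (125 per arm, ratio not stated), exponential event and loss times, exactly 5 years of follow-up unless noted.

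**1. The plan's own figure.** The hazard ratio is ln 0.98 / ln 0.92 = 0.242. Schoenfeld's formula for 90% power gives 4 × (1.960 + 1.282)² / (ln 0.242)² = 20.9, so 21 events. At a mean risk of 5% that is 420 patients before loss. With 250 patients and 20% loss about 11.2 events are expected, and power is 0.66 (Schoenfeld) or 0.53 (Freedman). The stated 90% therefore does not reproduce. That is a separate and larger matter than this point.

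**2. What a simple proportion would show.** With true 5-year risk p and loss q, let h = −ln(1−p)/5 and g = −ln(1−q)/5.
- Lost counted as successes: A = h/(h+g) × [1 − (1−p)(1−q)]
- Lost dropped: B = A / [A + (1−p)(1−q)]

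Worked case, p = 8%, q = 20%: 5h = 0.0834 and 5g = 0.2231. A = 0.2720 × (1 − 0.736) = 7.18%, and B = 0.0718/(0.0718 + 0.736) = 8.89%.

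| True risk | Loss | A | B |
|---|---|---|---|
| 8% | 20% | 7.18% | 8.89% |
| 2% | 20% | 1.79% | 2.24% |
| 8% | 30% | 6.75% | 9.48% |
| 8% | 10% | 7.60% | 8.41% |
| 2% | 10% | 1.90% | 2.11% |

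- Equal 20% loss: the true 6.0-point difference reads 7.18 − 1.79 = 5.4 or 8.89 − 2.24 = 6.65, about 6.7.
- Assumed loss of 30% (conservative) and 10% (surgery): it reads 6.75 − 1.90 = about 4.8, or 9.48 − 2.11 = 7.4.
- Equal true 8% rates with loss of 30% and 10%: a false gap of 7.60 − 6.75 = 0.85 or 9.48 − 8.41 = 1.07 points, in opposite directions.

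**3. Is the proportion test weaker?** Simulation with 6,000 trials, 125 per arm, 8% against 2%:

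| Loss (conservative / surgery) | Log-rank | Proportions, all randomised | Proportions, lost dropped |
|---|---|---|---|
| none | 0.61 | 0.61 | 0.61 |
| 20% / 20% | 0.55 | 0.54 | 0.56 |
| 30% / 10% (assumed) | 0.58 | 0.48 | 0.67 |

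With equal loss there is no meaningful difference in power. In the unequal row the two proportion versions move apart because their estimates are distorted in opposite directions.

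**4. Does the choice change conclusions?** With equal 20% loss, any two of the three analyses disagree on significance in about 2 to 4% of simulated trials. With 30% / 10% loss, the log-rank result and the 95% CI for the all-randomised proportions disagree in about 10%. The 95% CIs from the two proportion versions disagree with each other in about 14%.

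**5. Exploratory interactions.** Expected surgery-arm events are 125 × 1.79% = 2.2 at 5 years, or about 2.6 with 5 to 7 years of follow-up. For a subgroup that splits the arm in half, the Poisson chance that at least one half has no event is 1 − (1 − e^(−m/2))². This is 0.55 at m = 2.24 and 0.47 at m = 2.6. An ordinary interaction estimate is then infinite.

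**The case against.** The strongest reply is that the plan already contains what is asked for. A time-to-event analysis is planned, the withdrawal rule makes sense only for such an analysis, and the sizing section speaks of Kaplan-Meier rates. The success rates could be 5-year Kaplan-Meier rates, since the text does not say how they are estimated. In a condensed article, the estimator and its interval may properly be left to a fuller document.

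Much of this stands. A reader might infer that the plan has no method able to handle the 20% loss; the text does not support that. A reader might infer that logistic regression is the main comparison; it appears only for the exploratory interactions. A reader might infer that the analysis is less powerful than the one sized; the like-for-like simulation shows otherwise. Unequal loss is also an assumption, because the protocol assumes 20% in both arms. Even then the false gap of about 1 point is small beside the 95% CI half-width of about 5.4 points at 125 per arm: 1.96 × √(0.08×0.92/125 + 0.02×0.98/125). And sparse events would defeat an ordinary Cox interaction model just as they would a logistic one.

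What remains is not missing detail. The section sets the outcome comparison apart from the time analysis and elsewhere models the success rate by logistic regression, which suggests a binary reading. It attaches the time analysis to progression rather than to the event that was sized. The article thus states one test for sizing and a different lead comparison for analysis.

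**Conclusion.** The point holds in limited form. The sizing test and the lead analysis of the primary outcome are not matched, no analysis is ranked first, and the withdrawal rule fits only the one described as additional.

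If the success rates are simple proportions, the planned 6.0-point difference reads about 5.4 or 6.7 under the protocol's own 20% loss. With an assumed 30% against 10% loss, equal true 8% rates show a false gap of about 1 point. If the rates are Kaplan-Meier estimates, this distortion does not arise under the same assumption of loss unrelated to prognosis, and only the ranking and the definition of progression remain to be fixed. The figures rest on 1:1 allocation and exponential event and loss times.

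The harm is a possibly distorted estimate and an open choice of analysis by unblinded analysts. It is not lost power, nor a plan with no means of handling loss. This is an improvement that costs nothing, not a flaw that invalidates the design.

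**What to change.** In the Statistical analysis section:

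- Name the two-sided log-rank test on time from randomisation to first composite event as the primary analysis, with censoring at withdrawal.
- Report the difference in 5-year Kaplan-Meier event-free rates with a 95% CI, and a Cox hazard ratio.
- Define success as freedom from the composite event, and define progression in terms of that event.
- Optionally, use a Firth-penalised time-to-event model for the interaction analyses, which are already exploratory, because only about 2.2 to 2.6 surgery-arm events are expected.

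The cost is a change of wording. No new data, visits or patients are needed.

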### Patients

All patients with RA and atlantoaxial cervical spine involvement on conventional X-rays, CT or MRI of the cervical spine without neurological impairments will be asked to participate in the trial at one of the participating RA specialized hospitals. If patients with RA, aged 18–70 years old, have an AAS in the randomization range without neurological impairments (Ranawat I and II) without severe comorbidity, MRI incompatibility or previous cervical surgery, early surgical fixation will be compared with prolonged conservative treatment. The in- and exclusion criteria of the delphi trial are listed in table 3. Patients with neurological deficits as a result of cervical spine involvement will be followed in a cohort group.

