#### Secondary outcome parameters

1) 'Perceived recovery/deterioration.' This is a seven-point Likert scale measuring the perceived recovery or progression, varying from 'completely recovered' to 'worse than ever'.

2). The American Spinal Injury Association (ASIA) and International Medical Society of Paraplegia have developed a standard form for capturing clinical information when evaluating a patient who has had a spinal cord injury. The ASIA score is a motor and sensory quantifying score of both arms and legs [46]. The ASIA score will be used once neurological deficits have occurred.

3). The Disease Activity Score (DAS-28) is a classification used by many rheumatologists and is a measure of the overall disease activity of RA. In Europe the DAS is the recognized standard in research and clinical practice. For a good comparison of the severity and disability due to the RA inflammatory process between all patients in the two treatment groups of the different countries the DAS-28 will be used. The following parameters are included in the calculation: Number of joints tender to touch (TEN), Number of swollen joints (SW), Erythrocyte sedimentation rate (ESR), patient assessment of disease activity [47].

4). VAS pain will be measured of pain in the neck and occiput before randomization and during the follow up. Pain will be assessed on a horizontal 100 mm scale varying from 0 mm, 'no pain', to 100 mm, 'the worst pain ever' [48].

5) EuroQol classification system and VAS rating personal health [49]. A cost-utility analysis will be performed using QALY's based on the EuroQol questionnaire, which has been validated in many studies and is easy to fill out. Patients describe their general health status using the EuroQol classification system, consisting of 5 questions on mobility, self care, usual activities, pain/discomfort, and anxiety/depression. Patients also rate their personal health using a visual analogue scale (VAS) ranging from worst imaginable health to best imaginable health.

6) Short-Form 36 (SF-36). Quality of life will also be assessed using the RAND-36 questionnaire [50]. This is a generic health status questionnaire, which can easily be filled out at home. The questionnaire consists of 36 items on physical and social functioning.

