### Follow up

Follow up with clinical assessments and outcome measures will be assessed at baseline and after 3, 6, 12, 18 and 24 months. After two years the patient will be controlled once a year till eventually 10 years after randomization. During the follow up parameters will be registered to evaluate the quality of life, illness restrictions and neurological impairments. Direct and indirect medical costs will be calculated in each group.

Every control moment an X-ray of the cervical spine will be made (neutral/flexion/deflexion) except three months postoperatively. Prior to randomization and six months postoperatively a CT scan will be made to evaluate fusion and surgical stabilization. At fixed intervals and on clinical indication a MRI scan of the cervical spine will be performed. The clinical, neurological and radiological parameters will be registered on the follow up CRF. Data collection will take place per treatment center and will be gathered and analyzed at the LUMC in Leiden by the trial coordinator together with the statistical department and the epidemiological department of the VUMC in Amsterdam.

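### The change-score analysis does not secure each continuous outcome's own baseline as a covariate, and ASIA as scheduled has no baseline from which to compute a change

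*Protocol article*

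**What the plan says.** The Statistical analysis section of the protocol article defines the analysis variable: "Continuous outcomes are evaluated as change scores (differences between baseline measurement and each follow-up measurement". The next sentence reads: "Multivariable analyses are performed to adjust for the eventual differences between the groups at baseline in prognostic indicators". Shortly before these comes a baseline check: "Baseline comparability will be investigated by descriptive statistics to examine if randomization was successful". The covariates are not listed, and an outcome's own baseline value is not named among them.

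The baseline values are available. The Follow up section states: "Follow up with clinical assessments and outcome measures will be assessed at baseline and after 3, 6, 12, 18 and 24 months". For pain the secondary outcomes section is explicit: "VAS pain will be measured of pain in the neck and occiput before randomization and during the follow up".

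ASIA is treated differently. The same section says: "The ASIA score will be used once neurological deficits have occurred". The Patients section limits randomisation to those who "have an AAS in the randomization range without neurological impairments (Ranawat I and II".

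**The concern.** A change score fixes the weight given to baseline at exactly 1. Regression on baseline estimates that weight from the data. When the true slope is below 1, the change score subtracts too much: it adds noise, and it turns a chance imbalance at baseline into a shift of opposite sign at follow-up. Adding the baseline value as a covariate removes both effects. The gain in precision exists even when the arms are perfectly balanced, so adjustment that depends on seeing a difference may miss it.

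At stake is the precision of the secondary and other continuous outcomes: VAS pain, DAS-28, SF-36, EuroQol, the imaging measures, and the MDI when it is used as a score.

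For ASIA the difficulty is one of definition. Under its own rule it is not recorded at entry, so follow-up minus baseline cannot be formed. The patients who do have a score are selected by something that happens after randomisation.

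**Working it through.** **Inputs.** There is no figure in the plan to reproduce. Its only power statement, "A two-sided log rank test with an overall sample size of 250 patients, achieves 90% power at a 0.05 significance level", concerns the event outcome. The article gives no standard deviation, target difference or baseline/follow-up correlation r for any continuous outcome. I therefore assume r from 0.3 to 0.9. I take 250 patients less the 20% loss in the sample size section, which leaves 200, or 100 per arm if allocation is equal (also an assumption).

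**Precision.** With equal variances at baseline and follow-up, and in units of the outcome variance:

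- change score: 2(1−r)
- baseline-adjusted: 1−r² = (1−r)(1+r)
- ratio: 2/(1+r)

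The 200 patients analysed by unadjusted change scores then have the precision of 200 × (1+r)/2 patients analysed with baseline adjustment.

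**Imbalance.** Given a baseline difference d between arms, the expected follow-up difference is the treatment effect plus r·d. Subtracting d leaves the treatment effect plus (r−1)d. The table uses d = 0.2 SD as an illustration. The power column assumes a true difference of 0.4 SD with 100 per arm.

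| r | 2(1−r) | 1−r² | Ratio | Equivalent N of 200 | Shift at d = 0.2 SD | Power, change v adjusted |
|---|---|---|---|---|---|---|
| 0.3 | 1.40 | 0.91 | 1.54 | 130 | −0.14 SD | 67% v 84% |
| 0.5 | 1.00 | 0.75 | 1.33 | 150 | −0.10 SD | 81% v 90% |
| 0.7 | 0.60 | 0.51 | 1.18 | 170 | −0.06 SD | 96% v 98% |
| 0.9 | 0.20 | 0.19 | 1.05 | 190 | −0.02 SD | both near 100% |

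**Unequal variances.** Let k be the follow-up SD divided by the baseline SD, and work in units of the baseline variance. The change-score variance is k²+1−2rk and the adjusted variance is k²(1−r²). Their difference is (1−rk)². This is never negative, and it is zero only when rk = 1, for example r = 0.7 with k = 1.43. The direction of the result therefore does not depend on equal variances, but the ratios in the table do.

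**With baseline in the model.** Subtracting the baseline value from the response only lowers the baseline coefficient by 1; the treatment coefficient does not change. A check on one simulated data set gave 0.5221 for both the change and the follow-up value. The matter therefore turns on whether the covariate is included, not on which of the two is the response.

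**ASIA.** Randomised patients enter without neurological impairment, and ASIA is used only once a deficit exists, so no ASIA score is due at entry. The Follow up section says in general terms that outcome measures are assessed at baseline. If that includes ASIA, the two statements conflict. The subset with a score would also be small. With 125 per arm and the planned 5-year rates of 8% and 2%, one expects 125 × 0.08 = 10 and 125 × 0.02 = 2.5 patients with an event of any of the five types. Neurological deficit is one of those types, so patients with a deficit would number at most about this many.

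**The case against.** The strongest reply is that the plan does adjust. The sentence on multivariable analyses directly follows the one on change scores. If its models include the outcome's own baseline, the loss of precision and the imbalance shift both vanish. A condensed article may also leave its covariate list to an analysis plan that is not shown. This stands to the extent that the missing list is no finding, and a reader should not infer that the plan commits to raw, unadjusted change scores. What remains is what the article itself fixes: adjustment is aimed at differences between the groups at baseline, after a descriptive check of balance. That does not secure the baseline covariate when the arms look alike.

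Second, the size rests on assumptions. The ratio needs equal variances and an assumed r, and at r = 0.9 the excess is only 5%. Unequal variances are plausible for AADI, because entry restricts it to 5–12 mm and follow-up does not. This stands, and it is why the size is given as a range.

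Third, change scores are valid under randomisation. This also stands: the contrast is unbiased on average, and the shift (r−1)d is conditional on the imbalance that happens to occur.

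Fourth, a reader might infer that a biased between-arm ASIA comparison is planned. The article does not expressly plan one. Its wording equally fits describing deficits when they arise.

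**Conclusion.** The point holds as a cheap improvement to the analysis of the continuous outcomes, not as an error that invalidates them. If the outcome's own baseline is left out, the variance of the treatment effect is 5% to 54% larger for assumed r from 0.9 down to 0.3 under equal variances, and a chance imbalance d moves the estimate by (r−1)d. If the covariate is included, there is no loss.

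It would go too far to conclude that the trial's main result is at risk. The primary outcome is the occurrence of an event, and its analysis does not use these change scores.

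For ASIA, the scheduling rule and the general baseline statement need to be reconciled, and under the scheduling rule a change score does not exist. A between-arm test among patients with deficits would not be a randomised comparison, but the documents support no claim that such a test is planned.

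**What to change.** For every continuous outcome measured at baseline (VAS pain, DAS-28, SF-36, EuroQol, MDI as a score, imaging measures), model the follow-up value, or equivalently the change, on treatment and that outcome's baseline value. State that this covariate is prespecified and is included whatever imbalance is seen. A repeated-measures mixed model across visits is one way to do it.

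For ASIA, reconcile the rule in the secondary outcomes section with the baseline statement in the Follow up section. Exempt ASIA from the change-score analysis and report it descriptively among patients with deficits, with no between-arm test in that subset. Do not assign normal scores to the other patients. Ranawat II patients are eligible and, by the article's own description, can have subjective weakness, hyperreflexia and dysesthesia, while ASIA scores motor and sensory function.

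The cost is a few sentences of analysis wording. The baseline values are already planned, and no extra assessment is needed.
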